### **2.5.3 Drop-out criteria**

Subjects who voluntarily terminated treatment during the course of treatment; subjects who did not receive treatment according to plan, either due to poor compliance or non-cooperation; and subjects who were not suitable to continue the trial due to serious adverse reactions or appearance of other accompanying diseases.

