## **2.6 Sample size**

The number of subjects needed in each study group to test the primary hypothesis was determined based on previous clinical trials assessing spasticity in cerebral palsy children. A prior study by Auvichayapat [54] testing the effects of anodal tDCS on upper limb spasticity using Modified Ashworth Scale (MAS) found that a sample size of 46 individuals divided into two groups (1 mA a-tDCS [ $n = 23$ ], Sham a-tDCS [ $n = 23$ ]) had an effect associated with a power of 0.90 with an alpha level of 0.05 [57]. If the combined tPCS and TENS therapy in this study had a similar effect on our primary outcome measure of MAS, the authors determined that 60 participants (30 per condition) would be sufficient to provide a power of 0.90 with an alpha of 0.05, to which we will add 10 participants to compensate for possible dropouts, totaling 70 participants.

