## 2.8 Assessment

Evaluations using Modified Ashworth Scale (MAS) and Modified Tardieu Scale (MTS) will be conducted on all participants by two qualified rehabilitation doctors who have been involved in clinical work of pediatric rehabilitation for more than five years. The evaluators are blinded to the allocation of the children to the two groups and did not participate in the treatment of the subjects. A baseline evaluation and a post-treatment evaluation will be held. Both baseline and post-treatment evaluation will be conducted in a designated evaluation room that is spacious, quiet and bright, as follows:

- Baseline evaluation: three days prior to intervention
- Post-treatment evaluation: three days following last session of treatment
- Each scale will be repeatedly measured 3 times each time. Each score was the average of the three measurements.

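### Drop-out is defined by events after randomisation and the outcome visit is timed from the last session, so children who stop or miss treatment are planned as lost or mistimed data, possibly unequally between arms

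*Protocol*

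**What the plan says.** Protocol section 2.5.3 lists three routes to drop-out:

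- children who choose to stop the therapy partway through;
- "subjects who did not receive treatment according to plan, either due to poor compliance or non-cooperation";
- children "not suitable to continue the trial due to serious adverse reactions or appearance of other accompanying diseases".

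All three occur after randomisation. They concern treatment or fitness to continue; none is a refusal of further assessment.

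Section 2.6 sets 60 participants for the power claim and continues: "to which we will add 10 participants to compensate for possible dropouts, totaling 70 participants".

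Section 2.8 provides a baseline and a single later assessment, defined as "Post-treatment evaluation: three days following last session of treatment". It gives no time counted from randomisation or from the start of treatment.

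The arms carry different burdens. Under sections 3.1 and 3.2 both receive physical therapy five times a week for twelve weeks, and the Experiment arm alone has 60 additional 30-minute stimulation sessions. Section 4 has nurses observe all participants, but asks about side effects at the end of each session only in the Experiment group. It also ends treatment for any adverse event.

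Section 5 names the tests. It states neither who is analysed nor how drop-outs are handled.

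**The concern.** Stopping treatment and leaving follow-up are different events. A child who cooperates poorly or stops early can usually still be examined, and the randomised comparison needs that child's outcome. Section 2.5.3 merges the two under one label, and section 2.6 then compensates for the label with extra children, which makes sense only if drop-outs are expected to supply no outcome. Section 2.8 adds to the problem: a child who stops early is assessed either at a different time from the others or not at all.

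If losses fall unequally on the arms and are related to final muscle tone, the children left are no longer comparable between arms. Difference in burden is a reason to expect inequality. Section 1.1 adds that this population often has intellectual and cognitive impairment that makes active participation hard, so non-cooperation with an extra procedure is a realistic event. At stake are a biased estimate on MAS, the primary outcome, and a type I error above the stated 0.05.

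**Working it through.** **The plan's own figure.** Section 2.6: 60 + 10 = 70. As an inflation for lost outcomes, N/(1 − d) with d = 10/70 = 14.3% gives 60/(1 − 10/70) = 70. The figure reproduces, and it has the form used when drop-outs contribute no outcome.

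**Timing.** Treatment runs 12 weeks, so a child who finishes is assessed at about 12 weeks plus 3 days. A child whose last session falls at the end of week 3 would, read literally, be assessed 12 − 3 = 9 weeks before the others. The rules therefore give an early stopper a non-comparable outcome (section 2.8) or none (sections 2.5.3 and 2.6).

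**Opportunity for drop-out.** 5 sessions × 12 weeks = 60 stimulation sessions in the Experiment arm and 0 in the Control arm, on top of the same physical therapy schedule.

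**How large the bias could be.** From the protocol: 70 children allocated 1:1, so 35 per arm; 10 drop-outs; alpha 0.05. Assumptions, because the documents give no figures: no true effect, normal outcome with SD 1 (higher = worse tone), the split of the 10 between arms, and the correlation ρ between the tendency to drop out and a worse final outcome. Each child has a score L = ρX + √(1 − ρ²)·e, where X is the outcome and e is independent noise. The k children with the highest L in an arm are removed, and the completers are compared by a two-sided t-test. There were 40,000 simulated trials per scenario. A negative difference favours stimulation.

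| Drop-outs, Experiment/Control | ρ = 0: bias (type I error) | ρ = 0.3 | ρ = 0.6 | ρ = −0.3 |
|---|---|---|---|---|
| 5/5 | −0.002 (4.9%) | 0.001 (5.2%) | 0.001 (6.0%) | 0.001 (5.4%) |
| 7/3 | 0.001 (5.3%) | −0.052 (5.6%) | −0.106 (8.2%) | 0.053 (5.6%) |
| 8/2 | −0.001 (5.1%) | −0.082 (6.3%) | −0.158 (10.7%) | 0.079 (6.3%) |
| 10/0 | 0.000 (5.2%) | −0.139 (8.2%) | −0.279 (19.8%) | 0.139 (8.2%) |

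Consistency check: the bias should be proportional to ρ, and 0.279/0.139 = 2.0 = 0.6/0.3.

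**Reading the table.** Bias needs both an unequal split and a link with outcome. With a balanced split, or drop-out unrelated to outcome, it is zero within simulation error. If both are present and children doing worse leave more often, the bias favours stimulation; if children doing better leave, it goes against it.

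**Adverse events.** Section 2.5.3 refers to serious adverse reactions; section 4 ends treatment after any adverse event. The documents do not say whether a child whose treatment ends for a non-serious event is a drop-out.

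**The case against.** Several stronger readings are tempting, and the text does not support them.

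- A reader might infer that drop-outs are replaced by new recruits. They are not: the 10 are added in advance, and section 2.7 allocates one fixed list of 1 to n with no replacement step.
- A reader might conclude that the trial is a completer analysis. No section excludes drop-outs from analysis, and an analysis set may be defined in a statistical analysis plan that is not shown. Its absence from the protocol is not the finding.
- A reader might take every child with an adverse event to be a drop-out. Section 2.5.3 covers serious reactions only.
- A reader might take bias toward stimulation as established. It is not. TENS intensity is adjusted to each child's tolerance from 0 mA, which may limit intolerance. There is no sham, so disappointed control families may leave too; if worsening controls leave, the bias runs against stimulation. The single-arm drop-out scenario is the extreme of the range.
- Read literally, section 2.8 does give an early stopper an assessment, and a poorly compliant child who stays to the end is seen on schedule.

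All of this stands and narrows the point. It does not remove it. An assessment made weeks early is not comparable with one made at week 12. An analysis plan can choose whom to analyse, but it cannot recover outcomes that were never collected or were collected at the wrong time. Who is followed, and when, is fixed by this protocol.

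**Conclusion.** The concern holds in a limited form. Sections 2.5.3, 2.6 and 2.8 together plan for children who stop or miss treatment to be lost or assessed at a non-comparable time, and nothing secures their follow-up or their place in the allocated group. The difference in burden and in side-effect questioning makes unequal loss plausible, so completer bias is a real exposure. Its direction is plausibly, not certainly, toward stimulation.

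Its size cannot be derived from the documents. With 35 per arm, no true effect, 10 drop-outs and correlation 0.3 to 0.6 with worse outcome, a 7/3 split gives 0.05 to 0.11 SD and type I error of about 6% to 8%; 10/0 gives 0.14 to 0.28 SD and about 8% to 20%. A 5/5 split, or drop-out unrelated to outcome, gives no bias, and a reversed correlation reverses the sign. These splits and correlations are assumptions. The point should be fixed: the remedy is cheap and outcomes missed during the trial cannot be recovered.

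**What to change.** 1. In section 2.5.3, separate discontinuation of study treatment from withdrawal of consent to assessment. Only the second ends follow-up.
2. In section 2.8, assess every randomised child whose guardian has not withdrawn consent at one fixed time, 12 weeks plus 3 days from the start of treatment or the equivalent from randomisation, whatever number of sessions was received. Counting from randomisation also covers a child who never starts.
3. In section 5, make the primary analysis all randomised children in their allocated group, with completers as a sensitivity analysis. Report drop-out numbers and reasons by arm.
4. Reconcile section 2.5.3 (serious adverse reactions) with section 4 (any adverse event), and state which of these children count as drop-outs. Which rule applies is for the sponsor and investigators to settle.

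Cost: protocol wording and one MAS/MTS visit for each child who stops. The estimated effect may be slightly diluted by non-adherence. The sample size stays at 70; the 10 extra children then cover only outcomes that truly cannot be obtained.

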## **2.6 Sample size**

The number of subjects needed in each study group to test the primary hypothesis was determined based on previous clinical trials assessing spasticity in cerebral palsy children. A prior study by Auvichayapat [54] testing the effects of anodal tDCS on upper limb spasticity using Modified Ashworth Scale (MAS) found that a sample size of 46 individuals divided into two groups (1 mA a-tDCS [ $n = 23$ ], Sham a-tDCS [ $n = 23$ ]) had an effect associated with a power of 0.90 with an alpha level of 0.05 [57]. If the combined tPCS and TENS therapy in this study had a similar effect on our primary outcome measure of MAS, the authors determined that 60 participants (30 per condition) would be sufficient to provide a power of 0.90 with an alpha of 0.05, to which we will add 10 participants to compensate for possible dropouts, totaling 70 participants.

## **2.7 Randomization and Allocation Concealment**

Those who meet the eligibility criteria and with written consent obtained from their respective guardians to the participation of their children, will be randomly allocated to one of the two groups (Experiment Group and Control Group) using a simple random sampling method in accordance to China clinical research standards in “Methodology of Clinical Scientific Research of Integrated Traditional Chinese and Western Medicine (2nd edition)”. The Experimental Group will be treated with routine physiotherapy and combined tPCS and TENS therapy. The Control Group will be treated with routine physiotherapy only.

A number sequence will be first listed in the order of 1 to  $n$  (where  $n$  represents the total number of eligible participants). Stata 11.0 software will be used to generate another set of random numbers that is each assigned to one number in this number sequence 1 to  $n$  chronologically as they are generated. The number sequence 1 to  $n$  will subsequently be sorted based on the ascending values of the assigned random number, thereby re-ordering the number sequence. The first half of the re-ordered number sequence will be allocated to the Experimental Group while the bottom half will be allocated to the Control Group. Placement cards each written with a number from 1 to  $n$  and its corresponding group (either experimental or control) will be placed into opaque envelopes and sealed to ensure the concealment of the allocation. All  $n$  envelopes will be handed over to an administrator uninvolved in the random sampling process, who will give out the envelopes to the eligible patients entering the trial following pre-intervention evaluation. Each patient will then be allocated according to the group stipulated on the placement card.

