## 2.3 Study Design

This will be a prospective, controlled, equal randomization study (1:1), to be conducted at Guangzhou City Social Welfare Institute Rehabilitation Hospital in Guangdong Province, China (Fig 1).

[figure not shown]

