### **2.5.1 Inclusion criteria**

SCP was diagnosed according to diagnostic criteria of CP found in international guidelines [51]: children with CP aged 2–12 years of age, with GMFCS classification levels of III, IV, or V [52]; lower limb muscle tone in Grades I–IV in accordance to the Modified Ashworth Scale (MAS)[53]; no severe cardiopulmonary diseases; and voluntary participation and informed consent signed.

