## **Section 5: Statistical analysis**

SPSS v. 20.0 will be used for statistical analysis of the data. The data will be entered into Excel tables by double entry and checking to establish the database. The data of MAS and

MTS scales will be described in terms of means  $\pm$  standard deviation. If the data of MAS , and MTS scale did not conform to the conditions of normal distribution and homogeneity of variance, the Mann-Whitney test will be used; if the data of MAS and MTS scale did conformed to the conditions of normal distribution and homogeneity of variance, then independent sample t-test will be used. Pearson correlation analysis will be used for the correlation analysis between the GMFCS grade, gender and age and muscle tone after treatment in the Experiment Group. Either one-way ANOVA or Chi-squared test will be used for inter-group data comparison. A p-value less than 0.05 will be considered statistically significant.

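### GMFCS level, known at entry, is used neither in the allocation nor in the named between-group tests; adjusting for it with baseline score would recover precision at almost no cost

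*Protocol*

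**What the plan says.** Protocol Section 2.3 describes an "equal randomization study (1:1" design. Section 2.7 allocates "using a simple random sampling method" and gives the procedure in full. Eligible children are numbered in one list, the list is sorted by a random number, and "The first half of the re-ordered number sequence will be allocated to the Experimental Group"; the rest form the Control Group. No stratification, blocking or minimisation is mentioned. Arm sizes are therefore fixed, while the GMFCS make-up of each arm is left to chance.

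Section 2.5.1 admits children "with GMFCS classification levels of III, IV, or V", so the level is recorded at screening. Section 2.7 has an administrator "who will give out the envelopes to the eligible patients entering the trial following pre-intervention evaluation", so both the level and the baseline scale scores exist before allocation.

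Section 5 compares MAS and MTS by Mann-Whitney when normality or equal variance fails; when both hold, "then independent sample t-test will be used". It adds one-way ANOVA or chi-squared for comparing the groups and names no covariate. GMFCS enters once, in a Pearson "correlation analysis between the GMFCS grade, gender and age and muscle tone after treatment in the Experiment Group".

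**The concern.** The trial is small and spans three severity levels. If severity is related to muscle tone after treatment, two things follow.

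- Chance differences in severity between the arms add noise to the treatment comparison.
- In the one trial that is run, such a difference can imitate or mask part of the effect.

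The information needed to remove this noise is already collected, but neither the allocation nor the named tests use it. The correlation in Section 5 cannot serve that purpose, because it looks only inside the Experiment Group and says nothing about differences between arms. At stake are the efficiency of the primary comparison and how readily its estimate can be read if the arms turn out unequal in severity.

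**Working it through.** **Inputs from the protocol.** Section 2.6: 60 evaluable children plus 10 for dropout = 70, so 70/2 = 35 per arm (30 per arm evaluable); power 0.90, alpha 0.05. Section 2.7: one permutation cut in half. The protocol gives no figure for GMFCS imbalance and no expected GMFCS mix, so there is no planned value to reproduce and the mix must be assumed.

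**Step 1: chance imbalance in level V.** If K of the 70 children are level V, the number X in the Experimental arm is hypergeometric(70, K, 35). The between-arm difference is |2X − K|, and a gap of 6 children is 6/35 = 17 percentage points.

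| Assumed K | P(gap ≥ 6) | P(gap ≥ 8) |
|---|---|---|
| 20 | 2 × P(X ≤ 7) = 2 × 0.0926 = 0.185 | 0.063 |
| 30 | 2 × P(X ≤ 12) = 2 × 0.1135 = 0.227 | 0.090 |

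**Step 2: all three levels together.** Assumed III/IV/V mixes of 23/24/23, 14/21/35 and 10/25/35, with 200,000 random splits each. At least one level differs between arms by:

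- 10 points or more in 57% to 63% of lists
- 15 points or more in 26% to 33%
- 20 points or more in 22% to 25%
- 25 points or more in 8% to 9%

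The results change little across the mixes.

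**Step 3: effect on one trial's estimate.** Assume level V children sit 0.5 to 1.0 MAS grade above the others. A 6-child gap then moves the observed difference by 6/35 × 0.5 = 0.09 to 6/35 × 1.0 = 0.17 grade, in either direction.

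**Step 4: precision.** Adjusting for a covariate that explains a share R² of outcome variance multiplies the standard error by √(1 − R²). For GMFCS alone with assumed R² of 0.10 to 0.30, this is √0.90 = 0.949 to √0.70 = 0.837, a reduction of 5% to 16%. This is not the gain over a model that already contains baseline MAS. That incremental gain cannot be computed from the protocol and may be smaller.

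**Step 5: error rate and power.** Simulation at 30 per arm, 20 children at each level, 6,000 trials per setting. The effect is the one that 30 per arm detects with power 0.90, two-sided: d = (1.960 + 1.282) × √(2/30) = 0.837. The GMFCS-outcome correlation is assumed to be 0.3 / 0.5 / 0.7. Baseline score is not in these models.

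| Allocation and analysis | Type I error | Power |
|---|---|---|
| Single list, unadjusted t-test | 0.048 / 0.047 / 0.049 | 0.89 / 0.90 / 0.89 |
| Single list, GMFCS-adjusted | 0.048 / 0.050 / 0.046 | 0.91 / 0.96 / 0.99 |
| Stratified list, unadjusted t-test | 0.042 / 0.021 / 0.005 | 0.90 / 0.92 / 0.96 |
| Stratified list, GMFCS-adjusted | 0.052 / 0.045 / 0.045 | 0.92 / 0.96 / 0.99 |

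The planned test keeps its nominal level. Adjustment brings nearly all of the gain, under either list. Stratifying while keeping the unadjusted test makes that test conservative.

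**The case against.** The strongest reply is that simple randomisation with an unadjusted test is valid. Chance imbalance is already allowed for in the test's error rate, and Step 5 confirms this. That stands. A reader might infer that an imbalance would bias the trial or raise its false-positive rate; the procedure in Section 2.7 gives no ground for that.

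A reader might also infer that a sizeable severity imbalance is likely. Steps 1 and 2 do not support this. About four lists in five have a level V gap below 6 children, and a 20-point gap in any level arises in about one list in four.

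Nor does Section 5 state that GMFCS is related to outcome. It plans an exploratory correlation in one arm, listing gender and age beside GMFCS. The fair reading is that the plan thinks the relation worth examining.

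The size of the harm rests on assumptions about mix, grade difference and variance explained, and baseline MAS may already carry much of what GMFCS would add. That also stands, and it limits the claim about gain.

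Finally, covariate adjustment is often left to a statistical analysis plan, and one may exist. This carries less weight here, because Section 5 names the tests outright, so a later plan that adjusted would have to depart from it.

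Against stratified lists there is a further point. There is no sham (Sections 3.1 and 3.2), so treating staff know each allocation, and small permuted blocks within three strata would make later assignments easier to predict. The single list carries less of that risk.

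**Conclusion.** The point holds as a matter of efficiency, not as an error. Allocation ignores GMFCS level and the named between-group tests are unadjusted, although the level is known at entry. A gap of 6 or more level V children has a probability of about 19% to 23%, given 20 to 30 level V children among 70. In such a list the estimate would be displaced by about 0.09 to 0.17 MAS grade if level V children score 0.5 to 1.0 grade higher. Adjusting for GMFCS alone would cut the standard error by 5% to 16% at an assumed R² of 10% to 30%; the gain beyond baseline MAS is unknown. The facts about allocation and tests come straight from the protocol, while every magnitude depends on the stated assumptions.

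**What to change.** In Section 5, replace the unadjusted t-test or Mann-Whitney as the primary MAS comparison with a prespecified between-group model that includes treatment, baseline score and GMFCS level. ANCOVA would serve, with a rank-based or ordinal equivalent named in advance in case its assumptions fail. State beforehand how GMFCS enters the model. The unadjusted tests can stay as supporting analyses. The cost is a few lines of text and the extra model terms; no children, visits or measurements are added, and the change can be made even if the list has already been drawn, provided it is fixed before outcome data are seen.

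Stratifying the list by GMFCS is optional and adds little once the model adjusts. If it is done, the analysis must also adjust for GMFCS, and block sizes should be varied and concealed. The cost is three envelope series instead of one.

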## 2.8 Assessment

Evaluations using Modified Ashworth Scale (MAS) and Modified Tardieu Scale (MTS) will be conducted on all participants by two qualified rehabilitation doctors who have been involved in clinical work of pediatric rehabilitation for more than five years. The evaluators are blinded to the allocation of the children to the two groups and did not participate in the treatment of the subjects. A baseline evaluation and a post-treatment evaluation will be held. Both baseline and post-treatment evaluation will be conducted in a designated evaluation room that is spacious, quiet and bright, as follows:

- Baseline evaluation: three days prior to intervention
- Post-treatment evaluation: three days following last session of treatment
- Each scale will be repeatedly measured 3 times each time. Each score was the average of the three measurements.

